### Withdrawal and discontinuation

Participants are able to voluntarily withdraw at any time during the trial. Participants who fail to complete the study, regardless of time or reason, will be considered as dropouts. The last recorded data for these participants will be included in data analyses. Data obtained from participants who experience unrelated complications, such as substantial change in disease status, exacerbation of depression or commence medication that could potentially interfere with JDTLG, will be treated as invalid. Withdrawal due to adverse events will be distinguished from withdrawal due to insufficient response. All adverse effects will be analyzed at the endpoint of the trial regardless of whether they are deemed related to the trial medication or not. If a participant withdraws due to a serious adverse event, it will be reported in accordance with the reporting requirements. Where appropriate, data collected by these participants will be used in intention-to-treat analyses.

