### Intervention

Participants will be allocated to receive JDTLG or placebo for 8 weeks in addition to their usual conventional treatment (e.g., antiplatelet, lipid-lowering, antihypertensive, or antidiabetic therapy). The JDTLG and placebo granules (3.9 g/sachet) will be taken orally with warm water twice a day for 8 weeks. Product will be provided by China Resources Sanjiu Medical and Pharmaceutical Co., Ltd., Shenzhen, China (Production batch number: 161001 W). Analyses have shown that the quality of JDTLG is consistent with the Chinese Medicine Standards of the State Food and Drug Administration (SFDA). Active granules contain 3.9 g of JDTLG each, which is equivalent to 24 g of crude medicine. Placebo granules are composed of 10% crude JDTLG and 90% starch and are of identical appearance and smell as the active granules. Participants will be instructed to refrain from all other Chinese herbal decoctions or medicines used to treat PSD during the study. Participants can withdraw from the study and choose modern medical treatments, such as SSRI antidepressants, when their depressive symptoms worsen. All of the unused granules will be asked to be returned to the trial team and reasons of not taking the medicine will be recorded on the CRF.

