### Outcomes and measures

#### Primary outcome

The primary outcome is the effectiveness of JDTLG on reducing depression after 8 weeks of treatment. Efficacy defined as a decrease of 50% or more in the 17-item Hamilton Depression Scale (HAMD-17) score or clinical recovery (score < 7) [26].

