### Sample size calculation

This is an exploratory clinical trial designed to provide scientific rationale and feasibility for clinical phase II pilot study and, therefore, is not fully powered. A sample size of 80 participants will be recruited, with 40 participants in each treatment group. Results from this study will be used to for sample size calculations in future studies.

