### Statistical analysis

All of the data from this study will be analyzed by biostatisticians using SPSS 20.0 (IBM Corp., Armonk, NY, USA). Outcomes are based on the intention-to-treat analysis.

Baseline characteristics will be summarized by means of simple descriptive statistics and be compared between two study groups to assess covariate balance. The two-sample Student’s *t* test will be used for continuous variables and the chi-square test or Wilcoxon test will be used for categorical variables.

The primary analysis will be a comparison of the efficacy on depression between the two groups after 8 weeks of treatment. Pearson’s chi-squared test will be used to analyze the effective cases and logistic regression will be used to adjust for chance imbalances in the main prognostic variables between groups, such as age and gender.

Secondary analyses will include the improved cases in neurological function (NIHSS score reduction of ≥ 50% or the total score of 0–1), independence (mRS 0, 1, and 2), daily living (BI scores ≥ 90), and TCM syndrome. Secondary outcome analyses will be carried out according to standard statistical principles for comparison of parametric or non-parametric distributions as appropriate. Logistical regression analysis will be used to adjust for chance imbalances in the main prognostic variables between groups, such as age, NIHSS scores, BI scores, and TCM syndrome scores.

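### The withdrawal rule treats data as invalid after worsening depression or new interfering medication, contradicting intention-to-treat, and nothing says which rule prevails

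*Protocol article*

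**What the plan says.** Five statements in the protocol article bear on which data enter the primary analysis.

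- **Dropouts (Withdrawal and discontinuation).** Anyone who does not complete is a dropout, whatever the time or reason, and "The last recorded data for these participants will be included in data analyses".
- **Invalid data (same section).** The next sentence concerns data from participants with "unrelated complications, such as substantial change in disease status, exacerbation of depression" and from those who start potentially interfering medication. It ends: "exacerbation of depression or commence medication that could potentially interfere with JDTLG, will be treated as invalid".
- **Qualifier (same section, last sentence).** "Where appropriate, data collected by these participants will be used in intention-to-treat analyses".
- **Rescue (Intervention).** "Participants can withdraw from the study and choose modern medical treatments, such as SSRI antidepressants, when their depressive symptoms worsen".
- **Analysis principle (Statistical analysis).** "Outcomes are based on the intention-to-treat analysis", with no qualifier.

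On the endpoint, "The primary outcome is the effectiveness of JDTLG on reducing depression after 8 weeks of treatment". It is binary: a fall of at least 50% in HAMD-17, or a score below 7. The test is Pearson's chi-squared, with 40 participants per arm. On the use of the results, the Sample size calculation section says: "Results from this study will be used to for sample size calculations in future studies".

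**The concern.** Depression is the condition being treated, so its worsening is the primary outcome moving the wrong way. The article labels it unrelated before any case has been assessed. Starting an antidepressant is a likely consequence of worsening, and the plan itself offers that route, so both clauses can fall on the same people. These events happen after randomization and can be influenced by treatment, and most of the participants concerned would be non-responders at week 8.

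A participant who withdraws because depression worsened is covered at once by the dropout rule (keep the last score), the invalid-data rule (void the data) and the intention-to-treat statement (analyse everyone). These cannot all apply. If the invalid-data rule wins, the response rate is calculated after likely failures have been taken out of the denominator. Both rates are then too high, and the comparison is distorted whenever worsening differs between arms. If the choice is left open, it could be made after the data have been seen.

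**Working it through.** The article states no response rate, worsening rate, power or significance level, so it has no figure to reproduce. The contradiction rests on reading the text. The arithmetic below only shows what is at stake if the invalid-data rule is applied.

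**Inputs.** From the article: 40 per arm, binary response at week 8, Pearson chi-squared. Assumed: a true response rate of 40% (16/40) unless stated otherwise, all voided participants are non-responders, and a two-sided 5% test.

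**Formula.** Observed rate = responders / (40 − number voided).

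**No true difference, 16/40 in each arm (JDTLG v placebo)**

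| Voided | JDTLG | Placebo | Apparent difference |
|---|---|---|---|
| 0 v 0 | 16/40 = 40.0% | 16/40 = 40.0% | 0 |
| 4 v 4 | 16/36 = 44.4% | 16/36 = 44.4% | 0 |
| 4 v 2 | 16/36 = 44.4% | 16/38 = 42.1% | 2.3 points |
| 8 v 2 | 16/32 = 50.0% | 16/38 = 42.1% | 7.9 points |
| 2 v 8 | 16/38 = 42.1% | 16/32 = 50.0% | −7.9 points |

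**True difference of 15.0 points, 20/40 v 14/40**

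- Voiding 2 v 8: 20/38 = 52.6% v 14/32 = 43.8%, a difference of 8.9 points. A real effect is diluted.
- Voiding 8 v 2: 20/32 = 62.5% v 14/38 = 36.8%, a difference of 25.7 points. The effect is exaggerated.

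**False rejection.** Each participant is a responder (probability 0.40), worsened and voided (probability e) or another non-responder. The chi-squared statistic is computed without continuity correction. Exact enumeration of the 40-per-arm outcomes gives:

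| Worsening, one arm v the other | Rejection, worsened voided |
|---|---|
| nobody voided | 5.2% |
| 10% v 10% | 5.2% |
| 10% v 5% | 5.7% |
| 15% v 5% | 7.3% |
| 20% v 5% | 10.3% |

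Simulation agrees within about 0.1 point (5.6% for 10% v 5%; 10.3% and 10.4% in two runs for 20% v 5%). In the last row, 9.9 percentage points of the rejections favour the arm that worsened more, against 2.6 when everyone is kept. Keeping everyone in a denominator of 40 and counting the worsened as non-responders holds the rate at 5.2% whatever the worsening rates.

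**The case against.** A reader might infer that the plan orders these participants out of the primary analysis. The text does not go that far. The dropout rule covers every non-completer, including someone who leaves to take an SSRI, and keeps their last recorded data. The section's closing sentence allows intention-to-treat use, and the Statistical analysis section states intention-to-treat outright. This part of the objection stands: the defect is an unresolved contradiction, and the distortion follows only if the invalid-data rule is the one applied.

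It can also be said that the article's other use of the word invalid, in the TCM syndrome scale under Secondary outcomes, denotes the lowest response category, so the rule might mean that such participants count as failures. That reading is strained, because in the withdrawal section it is the data that are invalid. If failure was meant, saying so costs nothing.

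The section also separates withdrawal for adverse events from withdrawal for insufficient response. That shows that lack of response is recognised as a reason for leaving, but not how such a participant is counted.

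A reader might further infer that worsening mood would be lost from the safety analysis. The documents do not support that: all adverse effects are analysed whatever their relatedness, and all adverse events are followed.

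Finally, the trial is exploratory and described as not fully powered, so inflation of the type I error carries limited weight. That is fair. The lift in both response rates still matters, because the results are meant to size later studies.

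**Conclusion.** The point holds as a contradiction about which data enter the primary analysis. One stated rule voids data after outcome-related, post-randomization events, two others keep those participants in, and the article does not say which prevails. This is not detail left to an unseen analysis plan, since the article itself fixes the conflicting rules.

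The size is conditional on the invalid-data rule being applied and on assumed rates, with every voided participant a non-responder. Equal voiding of 10% lifts a 40.0% response to 44.4% in both arms and leaves the test size unchanged. A clear imbalance, 20% against 5%, produces a false difference of about 8 points and raises false rejection from 5.2% to about 10%. A mild imbalance, 10% against 5%, adds only about half a point to the error rate. No direction can be claimed: the rule flatters whichever arm worsens more, and if that is placebo it hides part of a real JDTLG effect. The text should be corrected, with moderate confidence about the practical impact.

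**What to change.** In Withdrawal and discontinuation:

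1. Delete the invalid-data rule from the primary analysis and state that all randomized participants are analysed as assigned.
2. Count as a non-responder anyone who withdraws for worsening depression or starts an antidepressant before week 8, whatever the last recorded score. Carrying forward a score taken before the worsening could otherwise register a response.
3. Keep the others on the list (other change in disease status, other interfering medication) in the analysis with their week-8 score or, if they drop out, their last recorded score.
4. Restrict the exclusion list to a secondary per-protocol analysis.
5. Report by arm how many worsened or started an antidepressant.

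No new visit or procedure is needed. Concomitant medication is already recorded to week 8, and withdrawal for insufficient response is already to be distinguished. The costs are a possibly lower response rate, a participant who improves on a new antidepressant counting as a failure, and a protocol amendment to the counting rule of the primary outcome while the trial is recruiting.

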### Intervention

Participants will be allocated to receive JDTLG or placebo for 8 weeks in addition to their usual conventional treatment (e.g., antiplatelet, lipid-lowering, antihypertensive, or antidiabetic therapy). The JDTLG and placebo granules (3.9 g/sachet) will be taken orally with warm water twice a day for 8 weeks. Product will be provided by China Resources Sanjiu Medical and Pharmaceutical Co., Ltd., Shenzhen, China (Production batch number: 161001 W). Analyses have shown that the quality of JDTLG is consistent with the Chinese Medicine Standards of the State Food and Drug Administration (SFDA). Active granules contain 3.9 g of JDTLG each, which is equivalent to 24 g of crude medicine. Placebo granules are composed of 10% crude JDTLG and 90% starch and are of identical appearance and smell as the active granules. Participants will be instructed to refrain from all other Chinese herbal decoctions or medicines used to treat PSD during the study. Participants can withdraw from the study and choose modern medical treatments, such as SSRI antidepressants, when their depressive symptoms worsen. All of the unused granules will be asked to be returned to the trial team and reasons of not taking the medicine will be recorded on the CRF.

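### The withdrawal section gives two incompatible data rules for participants whose depression worsens, and the one that treats their data as invalid conflicts, on its natural reading, with intention-to-treat

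*Protocol article*

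**What the plan says.** All references are to the protocol article.

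- **Intervention**, on worsening depression: "Participants can withdraw from the study and choose modern medical treatments, such as SSRI antidepressants, when their depressive symptoms worsen".
- **Withdrawal and discontinuation**, first rule: "Participants who fail to complete the study, regardless of time or reason, will be considered as dropouts". It continues: "The last recorded data for these participants will be included in data analyses".
- **Same section, next sentence**, second rule: "Data obtained from participants who experience unrelated complications, such as substantial change in disease status, exacerbation of depression or commence medication". The sentence ends: "exacerbation of depression or commence medication that could potentially interfere with JDTLG, will be treated as invalid".
- **Same section, further on**: "Withdrawal due to adverse events will be distinguished from withdrawal due to insufficient response", and in closing: "Where appropriate, data collected by these participants will be used in intention-to-treat analyses".
- **Primary outcome**: "The primary outcome is the effectiveness of JDTLG on reducing depression after 8 weeks of treatment". Response is a HAMD-17 decrease of at least 50% or a score below 7.
- **Statistical analysis** bases outcomes on intention-to-treat. **Sample size calculation** sets 40 participants per group, calls the trial exploratory and not fully powered, and says that its results will be used to size future studies.

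**The concern.** A participant whose depression worsens and who leaves to take an SSRI meets both rules. As a non-completer, this person's last recorded data go into the analysis. As someone with an exacerbation of depression, the same person's data are invalid. The closing sentence allows use in intention-to-treat analyses where appropriate but gives no criterion, so it does not rank the two.

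The second rule also describes exacerbation of depression as an unrelated complication, although depression is the condition under treatment and the primary outcome. If the rule means exclusion, removal is triggered by the outcome and can differ between arms. Treatment failures then leave the denominator, and the response difference can move in either direction. Because the results are meant to inform the size of later trials, the choice carries forward. If it is left open until after unblinding, it could also be made with the results in view.

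This is not detail that an analysis plan would ordinarily supply. The protocol fixes two rules, and an analysis plan that followed one would breach the other.

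**Working it through.** **Step 1. Which rule applies to whom.** Take one participant who worsens before week 8, withdraws and starts an SSRI.

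| Text | Applies? | Consequence |
|---|---|---|
| Dropout rule | Yes; it covers any time and reason | Last recorded data analysed |
| Invalid rule | Yes, through exacerbation of depression alone; that an SSRI could interfere with JDTLG is an inference and is not needed | Data invalid |
| Closing sentence | Perhaps | Used where appropriate, no criterion |
| Statistical analysis | Yes | Intention-to-treat |

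**Step 2. Do the rules give different primary results?** Inclusion requires a HAMD-17 score *b* of 7 to 24. A last score *s* ≥ *b* cannot be below 7, because *b* ≥ 7, and cannot satisfy *s* ≤ *b*/2. An enumeration of all baselines from 7 to 24 found no exception. A participant whose last score is at or above baseline is therefore a non-responder under the dropout rule, and absent from the denominator if the invalid rule excludes. (Visits are 4 weeks apart, so a last score may precede the worsening. The dropout rule then need not give non-response.)

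**Step 3. Size.** The protocol states no response or leaver rates, so there is no figure of its own to reproduce. Every count below is assumed except 40 per arm. Assume 22 active and 16 placebo responders, all among those who stay, with leavers non-responders under the dropout rule.

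All 80 kept: 22/40 − 16/40 = 0.550 − 0.400 = 0.150.

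Standard error: √(0.55×0.45/40 + 0.40×0.60/40) = 0.110. Then 1.96 × 0.110 = 0.216, so the 95% interval is about −7 to +37 points.

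Per-arm size for a next trial, with pooled variance under the null, two-sided 5% and 80% power, where p̄ = (p₁+p₂)/2:

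n = [1.96·√(2p̄(1−p̄)) + 0.842·√(p₁(1−p₁)+p₂(1−p₂))]² / (p₁−p₂)²

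| Leavers (active, placebo) removed | Response rates | Difference | Shift | n per arm |
|---|---|---|---|---|
| None (kept as non-responders) | 22/40 = 0.550; 16/40 = 0.400 | 15.0 points | – | 173 |
| 2, 6 | 22/38 = 0.579; 16/34 = 0.471 | 10.8 | −4.2 | 333 |
| 1, 3 | 22/39 = 0.564; 16/37 = 0.432 | 13.2 | −1.8 | 226 |
| 4, 4 | 22/36 = 0.611; 16/36 = 0.444 | 16.7 | +1.7 | 140 |

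(n is computed from the unrounded rates and rounded up.)

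**Step 4. Does the treatment of rescue also matter?** Suppose the 2 and 6 leavers were followed, and 1 active and 3 placebo participants responded on an SSRI and counted as successes. The difference would be 23/40 − 19/40 = 0.575 − 0.475 = 0.100. Removing the invalid rule is therefore not enough. The status of rescued participants has to be stated as well.

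**The case against.** **Invalid may mean treatment failure.** Under Secondary outcomes, *invalid* is the lowest category of TCM response, a reduction below 25%. If the withdrawal section used the word in that sense, worsening participants would count as failures, which is what intention-to-treat needs. This reading is possible. Against it, the subject of the sentence is the data, not the outcome or the treatment, so exclusion is the more natural meaning. What stands is that a reader should not take exclusion as proven.

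**The overlap may be narrow.** The invalid sentence is limited to unrelated complications, and withdrawal for insufficient response is named separately. Some leavers may therefore fall only under the dropout rule. That is fair, but exacerbation of depression is one of the sentence's own examples, and no boundary with insufficient response is drawn. Some overlap remains.

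**Rescue and lost follow-up.** A reader might infer from the Intervention section that anyone who takes an antidepressant must leave and is lost to follow-up. The text does not say so. The wording is permissive and protects participants in a placebo-controlled depression trial. No sentence forbids further visits, and Study visits and procedures gives the schedule to week 16 without exception. The figures above measure the conflict between data rules, not lost follow-up.

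**The counts are invented and the trial is a pilot.** Both are true. A reader who saw only 173 against 333 per arm might conclude that the wording doubles the next trial. That is the most extreme of the three cases; the others give 226 and 140, the last in the opposite direction. Chance alone would dominate any sizing based on an interval of about −7 to +37 points.

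**Conclusion.** The point holds as a contradiction within Withdrawal and discontinuation and, on the natural reading of *invalid*, as a conflict with the intention-to-treat statement. Excluding participants because the primary outcome worsened is a wrong rule, not a missing detail. The documents do not establish that data will in fact be discarded, that follow-up will be lost, or which way a bias would run.

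Under the assumed counts the difference moves from 15.0 points to between 10.8 and 16.7, a shift of −4.2 to +1.7 points. This is modest beside a standard error of about 11 points, and small if few participants leave. The size of a next trial would range from about 140 to 333 per arm around 173. These results rest on 22 and 16 responders of 40, on leavers being non-responders, and on the leaver counts shown. The protocol gives none of these. The correction should be made because it is cheap and is best fixed before unblinding. Confidence is medium.

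**What to change.** In Withdrawal and discontinuation, delete the sentence that treats data as invalid. In its place, state that all randomised participants stay in the intention-to-treat analysis, and that worsening which leads to withdrawal or to starting an antidepressant before week 8 counts as non-response in the primary HAMD-17 analysis. This takes a short amendment. The article reports the trial as still recruiting, so the rule can be set for all participants before unblinding.

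As a cheap addition, not the correction of an error, the Intervention section can invite participants who stop the granules or start an antidepressant to the visits already planned to week 16. Reminder calls and a transport allowance are already provided under Compliance and retention, and access to antidepressants is unchanged. The cost is a site instruction and a few more visits, and some participants will still decline.

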### Outcomes and measures

#### Primary outcome

The primary outcome is the effectiveness of JDTLG on reducing depression after 8 weeks of treatment. Efficacy defined as a decrease of 50% or more in the 17-item Hamilton Depression Scale (HAMD-17) score or clinical recovery (score < 7) [26].

#### Secondary outcomes

Improvement in neurological function at each appointment throughout the trial. Efficacy will be determined by a reduction of ≥ 50% or the total score of 0–1 in the 15-item National Institute of Health Stroke Scale (NIHSS) score (scores range from 0 to 42, whereby higher scores indicate a more severe neurological deficit) [27]The improvement in independence at each appointment as measured by a modified Rankin Scale (mRS) at each appointment throughout the trial (scores on this scale range from 0 to 6, with higher scores indicating greater disability) [28]The proportion of participants with a Barthel Index (BI) score of ≥ 90 at each appointment throughout the trial. The BI is used to evaluate the activities of daily living, ranging from 0 to 100, whereby higher scores indicate increased independence [29]The improvement of TCM syndrome at each appointment as measured by the reduction (reduction = (before treatment score − after treatment score)/before treatment score × 100%) in the following scale: clinical cure: reduction > 75%, markedly effective: reduction 51–75%, effective: reduction 25– 50%, invalid: reduction < 25% [30]

